## Abstract

**Background:**

The World Health Organization leads a global strategy to promote the initiation and maintenance of breast-feeding.

Existing literature shows that education and supportive interventions, both for breast-feeding mothers as well as for healthcare professionals, can increase the proportion of women that use exclusive breast-feeding, however, more evidence is needed on the effectiveness of group interventions.

**Methods:**

This study involves a community-based cluster randomised trial conducted at Primary Healthcare Centres in the Community of Madrid (Spain). The project aims to evaluate the effectiveness of an educational group intervention performed by primary healthcare professionals in increasing the proportion of mother-infant pairs using exclusive breastfeeding at six months compared to routine practice.

The number of patients required will be 432 (216 in each arm). All mother-infant pairs using exclusive breastfeeding that seek care or information at healthcare centres will be included, as long as the infant is not older than four weeks, and the mother has used exclusive breastfeeding in the last 24 h and who gives consent to participate.

The main response variable is mother-infant pairs using exclusive breast-feeding at six months.

Main effectiveness will be analysed by comparing the proportion of mother-infant pairs using exclusive breast-feeding at six months between the intervention group and the control group. All statistical tests will be performed with intention-to-treat. The estimation will be adjusted using an explanatory logistic regression model. A survival analysis will be used to compare the two groups using the log-rank test to assess the effect of the intervention on the duration of breastfeeding. The control of potential confounding variables will be performed through the construction of Cox regression models.

**Discussion:**

We must implement strategies with scientific evidence to improve the percentage of exclusive breast-feeding at six months in our environment as established by the WHO. Group education is an instrument used by professionals in Primary Care that favours the acquisition of skills and modification of already-acquired behaviour, all making it a potential method of choice to improve rates of exclusive breast-feeding in this period.

**Trial registration:**

The trial was registered with ClinicalTrials.gov under code number NCT01869920 (Date of registration: June 3, 2013).

## Background

### Feeding newborns: The benefits of breast-feeding

Breast-feeding is the natural way to feed newborns, and human milk is the best-adapted food for their nutritional needs. Breast-feeding (BF) is considered the most adequate way to feed newborns as it provides all of the nutrients that they need to grow and develop in optimal conditions [1]. The World Health Organization (WHO) defines three types of breast-feeding [2]: exclusive breast feeding (EBF), when the infants receive only breast milk, accepting the use of rehydration salts, drops, syrups, vitamins, minerals or medicines; predominant breast-feeding (PBF), when water or water-based liquids and/or fruit juices are added to that included in EBF; and complementary feeding (CF), when any solid or liquid foods, including formula and non-human milk, are added.

BF presents various advantages for newborns, their families and the society in general, taking into account not only the health benefits, but also those that affect social, economic and environmental areas. The short-term benefits for newborns include a better nutritional and immunological state, better intestinal function, and a better establishment of attachment and increased psychological wellbeing [3, 4]. On the long-term, it decreases the risk of diabetes mellitus, obesity, heart disease in adults, certain allergy and inflammatory diseases, and it influences neurocognitive development [5–10]. For mothers, on the short-term it favours uterine involution, weight loss, decreased risk of uterine haemorrhaging, anaemia, hypertension and post-partum depression. On the long-term it acts as a protective factor against the risk of osteoporosis and breast and ovary cancer [4].

Among the social, economic and environmental benefits, BF incurs less costs both for families as well as for health systems while it also decreases the amount of residues and consumption of energy [11].

### Recommendations regarding the promotion of breast-feeding

Efforts are currently being made, both in the health sector as well as in non-health sectors, to promote the initiation and maintenance of BF. A global strategy led by the WHO has been launched that manifests the importance of nutrition in the first months and years of life and the fundamental role that correct feeding practices play in achieving optimal health. It also highlights the need to create comprehensive national policies that guarantee that health services protect, foment and support BF and opportune and adequate complementary feeding without interruption of BF. As a global Public Health strategy, EBF is recommended during the first six months of life, with posterior introduction of complementary feeding while continuing with BF up to 2 years of age or more if the mother would like to [12, 13].

Breast-feeding is a natural act and a learned behaviour that is possible for most mothers as long as they have adequate information, support from their families, communities and healthcare systems, as well as protective public policies for BF [12]. The promotion of BF must also incorporate a cultural focus that takes into account the effect that family environments can have, especially from mothers, grandmothers and partners [12, 14].

### Prevalence of breast-feeding in developed countries: Associated factors

In spite of the broad dissemination of recommendations to promote EBF and its benefits, only 35% of newborns around the world receive EBF after the first three or four months of life [15]. The rates are much lower than those set out by the WHO in European countries, and specifically, in Spain the rates are similar to the rest of the developed countries, with 24.72% EBF at six months, and slightly lower in the Region of Madrid (23.54%) [16].

In Spain the average length of breastfeeding is around 3–5 months. The greater number of abandonments of EBF takes place during the first 4 weeks, (sometimes up to one third of cases) and between the 3rd and 4th months of life, which coincides with the imminent return of the mother to work [17–20].

According to the results of an observational study in Spain the factors that influence the continuity of EBF up to six months are diverse: lack of confidence to breast-feed, pain, suction problems, cracks, infections, ingurgitation, mastitis, baby crying, type of birth, execution of early skin to skin contact, bad experience with prior breast-feeding, comments by family members and/or friends, aspects related with going back to work, and the socio-economic and education level of the mother [21, 22]. Other authors point out the possible effect that the model of the breast-feeding mothers’ mothers, women that lived during periods of setbacks regarding the prevalence of breast-feeding, many of whom most likely did not breast-feed, could have on the breast-feeding mother’s [14].

### Strategies to foment breast-feeding

To improve breast-feeding rates, strategies directed at professionals, breast-feeding mothers and those around them are being implemented.

The WHO and UNICEF launched the BFHI (Baby Friendly Hospital Initiative) strategy in 1991 with the objective to encourage hospitals, health departments and maternity wards to adopt practices that protect, promote and support EBF from birth [23]. Since conception, the strategy has spread into other healthcare settings in different countries.

On a national level (in Spain), a BFHI Healthcare centre strategy was created, adapting the aforementioned to the reality of Primary Healthcare [24]. The National Sexual and Reproductive Health Strategy of the Ministry of Health in 2010 included the promotion of BF [25].

On a regional level, the Health Department of Madrid and UNICEF withhold an agreement of collaboration to execute and consolidate changes in clinical practice following the criteria set forth in the BFHI initiative. Breast-feeding promotion committees have been created to implement the recommended good practices, EBF culture is being promoted and primary healthcare and hospital professionals of the Region of Madrid are being trained.

In primary healthcare, within the framework established by the Standardized Service Portfolio, individual interventions have been implemented to foment BF that are similar to those executed and evaluated in other regions in Spain [26]. Also, with the Health Promotion and Prevention Plan of the General Directorate of Primary Healthcare, the objective of promoting and supporting breast-feeding is included, encouraging its use during the first six months of life [27].

Two Cochrane reviews were published in 2008 related to BF.

The review by Dyson L, McCormick F y Renfrew MJ on interventions to promote the initiation of breast-feeding included seven studies with 1388 women and its results reflected the fact that education on breast-feeding had a significant effect on the increase of the rates of initiation compared with habitual practices (RR 1.53; CI of 95%: 1.25 to 1.88) [28].

The review by Britton C et al. on support for breast-feeding included 34 controlled, randomized and quasi-randomized clinical trials that compared the additional support for mothers that breast-fed with habitual practices, on a sample of 29,385 mother-child pairs from 14 countries. The results reflected that all of the forms of additional support analysed together showed an increase in the duration of any type of breast-feeding (RR of interruption of BF before six months of 0.91; CI of 95%: 0.86 to 0.96). All of the forms of additional support together had a greater effect on the duration of EBF than on any BF type (RR 0.81; CI of 95%: 0.74 to 0.89). Professional and non-professional support together significantly prolonged the duration of any BF (RR before 4 to six weeks 0.65; CI of 95%: 0.51 to 0.82; RR before 2 months 0.74; CI of 95%: 0.66 to 0.83). EBF was significantly prolonged with training by the WHO/UNICEF (RR 0.69; CI of 95%: 0.52 to 0.91). The review also concluded that more evidence is needed on the effectiveness of group interventions [29]. Specifically, the interventions that have shown to be effective to increase EBF on the short- and long-term include any form of support provided by healthcare professionals and non-healthcare professionals, individual interventions with an education or supportive component, and combined interventions related with pregnancy and the immediate post-partum period [29–32].

In the Region of Madrid, a clinical trial in Primary Healthcare (PHC) has been conducted to evaluate a strategy of implementation of clinical practice guidelines for BF directed at professionals. The experimental intervention has achieved an improvement in the rates of EBF at six months of 16% [33].

A multidisciplinary group of experts from the General Directorate of Primary Healthcare has designed an education project for group health that uses the promotion of BF as a medium to improve mother-infant health. As concluded in the Cochrane review by Britton C, more evidence is needed on the effectiveness of group interventions.

Our research proposal is The PROLACT study, which aims to measure the effectiveness of an educational group intervention in Primary Healthcare Centres.

By evaluating the effectiveness of this type of intervention, we will be able to produce rigorous projects that guarantee attainment of the proposed objectives while also finding out the results produced in the patients.

BF is a human behaviour that is greatly influenced by that which occurs in the community to which a mother belongs, and the effect can be contaminated from one mother to another. Likewise, when a professional is trained, it is rare that they would have an attitude unlike that of the mothers. Because we consider inevitable a ‘contamination’ effect of influence on each other between professionals working in the same centre, a cluster design has been chosen so that the interventions that do or do not take place will include all the professionals in each Primary Healthcare Centre (PHCC).

## Methods/design

### Objectives

The primary objective of this study is to evaluate the effectiveness of an educational group intervention in primary healthcare, compared to habitual practice (usual care) in increasing the proportion of mother-child pairs that use EBF up to six months of age.

The secondary objectives are:To compare the effectiveness of an educational group intervention in primary healthcare with usual care to increase the proportion of mother-child pairs that use PBF up to six months of age.To describe women’s adherence and degree of satisfaction with the educational group intervention.To describe the reasons for abandonment of breast-feeding in both study groups. To describe the reasons of breastfeeding abandonment in both study groups.To explore the predictive factors of maintenance EBF at six months of age.

### Design of the study

This study is a community, multicentre, parallel clinical trial, randomised by clusters, that compares usual care and an education strategy performed by primary healthcare professionals. The intervention will be carried out with mother-infant pairs in ten PHCCs in the Community of Madrid (Spain).

The randomization units will be the PHCCs (clusters). The units of analysis are the mother-infant pairs attended to by the PHCCs. This design by clusters minimises possible contamination effects between centres.

### Subjects of the study

Mother-infant pairs using EBF, that seek care or information at any PHC consultation before the first month of life of the newborn and that give their consent to participate in the study.

#### Inclusion criteria

Professionals of the randomization unit (CS):
Minimum of 2 years working as a professional in PHC.Have no intention of transferring during the study period.Provide healthcare to the infant population within their daily healthcare workload.Sign the researcher agreement.

Mother-infant dyad:
Mothers of full-term newborns and that use EBF ≥ 18 years of age at the selection visitFull-term newborns (≥ 37 weeks of gestation), with a birth weight > 2.5 kg and with the newborn’s age ≤ 4 weeks.

#### Exclusion criteria

Professionals of the randomization unit (CS):
Those that reject participation in the study.

Mother-child pairs:
Clinical conditions of the mother that contraindicate breast-feeding: active tuberculosis, active chicken pox, active Herpes lesions on breasts, Chagas disease; human immunodeficiency virus (HIV); human T-lymphotropic virus (HTLV) I and II; substance abuse; mother in treatment with radioactive isotopes or chemotherapy or antimetabolite drugs.Clinical conditions of the child that complicate or impede breast-feeding, orofacial malformations.Clinical conditions of the child that contraindicate breast-feeding: classic galactosemia (galactose-1-phosphate uridyltransferase deficiency) in newborns.Infants that have been initiated on complementary feeding.Women that do not consent to participating in the study.Impossibility of the mother to come to the visits proposed for the conduction of the study.Difficulties with the language that impede or complicate communication between the mother and the healthcare professionals.Women that are participating in another research study during the study period.

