### Randomisation

The randomisation unit will be the healthcare centres.

An independent statistician will carry out the randomised allocation to form groups of the same size from a list of the participating healthcare centres.

Posteriorly, within each unit, the mother-infant pairs will be selected by consecutive sampling, until the number is reached to form the cluster. Figure 1 describes how the pairs are recruited. During the consultations, the mothers will be informed about the study and asked if they would like to participate. All mothers that would like to have to sign a consent form and it will be confirmed that they meet all inclusion/exclusion criteria.

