### Intervention

The healthcare professionals will carry out the recruitment, they will collect the study variables, apply the assigned intervention and perform all follow-up (consultation and/or telephone). Each one of them will only carry out one type of intervention: experimental or control. To avoid the differences in the measurement of variables and the application of the intervention as much as possible, previous training will be executed.

The organization and functioning of the health services will not be altered significantly to carry out the study, as the control intervention is the habitual practice and the intervention for the treatment group will be planned and conducted just like any other educational group intervention in the core of the primary healthcare team. The Working Plan is shown in Table 1.

**Table 1 Tab1:** Project Working Plan

Visit	Randomisation:2 months before visit 1	Trainig: 1–2 months before visit 1	Visit 1: < 1 month after birth	Visit 2: 2 months after birth	Visit 3: 3 months after birth	Visit 4: 4 months after birth	Visit 5: 5 months after birth	Visit 6: 6 months after birth
Study procedure***s***								
Randomisation	**X**							
Professional training		**X**						
Informed consent			**X**					
Recruitment			**X**					
Demographics			**X**					
Telephone contact				**X**	**X**	**X**	**X**	**X**
Interventions								
Standard practice				**X**		**X**		**X**
PROLACT intervention			**X**		**X**		**X**	
Outcomes measures								
EBF			**X**	**X**	**X**	**X**	**X**	**X**
PBF			**X**	**X**	**X**	**X**	**X**	**X**
CF			**X**	**X**	**X**	**X**	**X**	**X**
Reasons for abandoning breastfeeding			**X**	**X**	**X**	**X**	**X**	**X**
Acceptability of intervention			**X**					
Adherence			**X**		**X**		**X**	
Satisfaction							**X**	

The Standardized Services Portfolio for Primary Healthcare of the Community of Madrid defines four services of assistance to the supervision and development of the infant population. These services are the promotion of health habits, monitoring of development, systemic vaccinations and early detection of childhood problems.

These services are carried out transversally throughout the scheduled revisions [available at http://www.madrid.org/cs/Satellite?c=CM_Publicaciones_FA&cid=1142521116585&idConsejeria=1109266187266&idListConsj=1109265444710&idPagina=1343067104390&language=es&pagename=ComunidadMadrid%2FEstru].

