#### Control group (usual care)

Usual care includes individual counselling about the benefits of maintenance exclusive breast-feeding during the first six months of the baby and about the introduction of complementary food after that. The mother should attend to the PHC at least twice, once before six months of age and another between six and 12 months of age.

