#### Intervention group (educational group intervention)

This is an educational group intervention based on the workshop on breast-feeding designed by the expert group of the General Directorate of Primary Healthcare of the Madrid Health Department. It is structured in six weekly sessions of 120 min each. Its objectives are the acquisition, reinforcement and/or consolidation of the necessary knowledge and skills to initiate and maintain EBF as the newborns feeding, as well as the development of a positive attitude regarding breast-feeding. It consists of theoretical and practical content with the active participation of the mothers in the discussion group and the learning of skills through the direct practice of breast-feeding.

The activities will begin around the first month of life of the child (the maximum peak of abandonment according to existing studies) [20–22, 24] and it will take six weeks.

The mothers will be offered during the training session the possibility to come with the person that most influences their decision to breast-feed (social support) [15, 17].

Follow-up will be conducted through regular revisions according to the protocol and telephone calls to collect the study variables.

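### The exclusion for mothers who cannot come to the study visits is applied after allocation by unmasked staff and can be read as requiring workshop attendance in intervention centres only

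*Protocol article*

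**What the plan says.** All references are to the Protocol article.

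- **The criterion (Exclusion criteria).** Pairs are excluded for "Impossibility of the mother to come to the visits proposed for the conduction of the study". The visits meant are not listed there, by arm or in common.
- **Allocation comes first.** Table 1 (Intervention) has "Randomisation:2 months before visit 1". Under Randomisation, "Posteriorly, within each unit, the mother-infant pairs will be selected by consecutive sampling, until the number is reached to form the cluster". At that consultation "it will be confirmed that they meet all inclusion/exclusion criteria".
- **The recruiters know the arm.** Under Intervention, "The healthcare professionals will carry out the recruitment, they will collect the study variables, apply the assigned intervention and perform all follow-up", and each professional delivers one arm only. Masking says that the intervention cannot be masked; blinding applies to the analysts.
- **Attendance differs by arm.** The workshop: "It is structured in six weekly sessions of 120 min each", beginning around the first month of life. Usual care: "The mother should attend to the PHC at least twice", with one of those attendances before six months of age.
- **Visits and treatment share one table.** Table 1 puts PROLACT delivery and adherence at Visits 1, 3 and 5, and standard practice at Visits 2, 4 and 6. Telephone contact is at Visits 2 to 6, and feeding outcomes are recorded at every visit, with no split by arm.
- **Analysis.** The primary comparison is Fisher's exact test by intention-to-treat. Logistic regression follows if confounders are found to be unbalanced.

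**The concern.** In a cluster trial that recruits after allocation, an eligibility rule protects the comparison only if it means the same in both arms. This one turns on what the mother is asked to attend, and that is not the same. If staff in an intervention centre count the group sessions among the proposed visits, a mother who cannot manage them is excluded there, while a similar mother in a control centre is enrolled.

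If mothers who cannot attend are also less likely to be exclusively breast-feeding at six months, the intervention arm starts with a better prognosis. The primary proportion would then differ with no effect of the workshop. Mothers who were never enrolled are in no analysis set, so intention-to-treat cannot bring them back. The limitations in the Discussion cover volunteering professionals, motivated control centres, unblinded self-report, differences in delivery and clustering. They do not cover differential recruitment of mothers.

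**Working it through.** **1. The plan's own figure.** Inputs from Sample size: 24% control rate, a rise of 15 points to 39%, 5% type I error (taken as two-sided), 80% power.

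n = [1.96·√(2·0.315·0.685) + 0.8416·√(0.24·0.76 + 0.39·0.61)]² / 0.15² = 149.4, so 150 per arm. Design effect 1 + 29·0.01 = 1.29; 150·1.29 = 193.5, so 194. Then 194/0.90 = 215.6, so 216 per arm and 432 in all. The stated size reproduces, and the point is not about it.

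**2. What the criterion can mean.**

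| Reading of the visits | Intervention centre | Control centre |
|---|---|---|
| Outcome-collection contacts only | Visit 1 and telephone contacts | The same |
| Everything the mother is asked to attend | The above plus six sessions, 6 × 120 min = 12 hours | The above plus routine attendance |

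The first reading is arm-neutral and the second is not. The text does not choose between them. By linking PROLACT delivery and adherence to numbered visits, Table 1 keeps the second open.

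**3. What the second reading could do.** Assumptions, none of them from the documents except the 24%: there is no true effect; all-comers have a six-month rate of 24%; a share f cannot attend the sessions and is excluded in the intervention arm only; the rate in that share is q.

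Intervention-arm rate = (0.24 − f·q)/(1 − f). Spurious gain = f·(0.24 − q)/(1 − f).

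The chance of p < 0.05 is a normal approximation with 194 analysed per arm, reduced by the design effect to 194/1.29 = 150.4.

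| f | q | Intervention-arm rate | Spurious gain (points) | Share of 15 points | Chance of p < 0.05 |
|---|---|---|---|---|---|
| 10% | 18% | 24.7% | 0.7 | 4% | 5.2% |
| 10% | 12% | 25.3% | 1.3 | 9% | 5.8% |
| 10% | 6% | 26.0% | 2.0 | 13% | 6.9% |
| 20% | 18% | 25.5% | 1.5 | 10% | 6.0% |
| 20% | 12% | 27.0% | 3.0 | 20% | 9.2% |
| 20% | 6% | 28.5% | 4.5 | 30% | 14.3% |
| 30% | 18% | 26.6% | 2.6 | 17% | 8.1% |
| 30% | 12% | 29.1% | 5.1 | 34% | 17.2% |
| 30% | 6% | 31.7% | 7.7 | 51% | 32.0% |

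Example: f = 0.30, q = 0.06 gives (0.24 − 0.018)/0.70 = 0.317, a gain of 7.7 points.

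**The case against.** The strongest reply is that the visits are simply the common schedule. The article calls workshop meetings sessions and numbers its visits 1 to 6 in one table for both arms. It treats session attendance as an adherence outcome, says mothers will be telephoned and invited to the sessions, and analyses by intention-to-treat. On that reading a non-attender is already enrolled and counted as non-adherent. This is a fair reading and it may be the intended one. It does not settle the matter, because Table 1 ties some of those visits to PROLACT delivery and the staff left to interpret the wording know their arm.

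Consecutive sampling and baseline adjustment also help. Sampling limits free choice among eligible mothers but does not stop an exclusion from operating differently by arm. Adjustment could use breast-feeding intention, self-efficacy, education, income and work situation. However, it is conditional on observed imbalance and cannot reach unmeasured commitment.

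Three further points stand:

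- A reader might infer that the rule screens out mothers returning early to work. The timing fits poorly: sessions starting at about one month and lasting six weeks end at about 2.5 months, whereas the Background links the return to work with stopping in the third to fourth month. The criterion also speaks of impossibility, not reluctance.
- The two routine attendances describe the usual-care service and are not a list of study visits, so setting 12 hours against two attendances overstates what the text fixes.
- A mother unwilling to attend can decline consent after allocation, and rewording one exclusion does not change that.

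The article is condensed and its recruitment figure is not shown, so a definition of visits or a screening log may exist elsewhere. The point is therefore not that these are missing, but that the printed criterion can work differently by arm within the printed design.

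**Conclusion.** The point holds as a risk created by ambiguous wording. It is stated outright that eligibility is confirmed after allocation, by unmasked staff who deliver one arm. That the criterion can exclude on session attendance in one arm only follows from its wording together with Table 1 and the workshop description.

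A reader might go further and conclude that the rule does select more committed mothers into the intervention arm, or that the bias amounts to several points. The documents support neither. They do not show how staff would apply the rule, how many mothers could not attend, or how those mothers would fare. The likely direction favours the intervention, on the assumption that mothers unable to attend have lower six-month rates.

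The size is unknown. The calculated 0.7 to 2.0 points at 10% excluded, and 1.5 to 7.7 points at 20% to 30%, assume exclusion in the intervention arm alone, which is the extreme case. They also take 24% as the rate in mothers who are already breast-feeding exclusively at enrolment. At the low end the effect on the primary test is negligible. At the high end it is about half the target effect. It is worth correcting because it touches the primary comparison and cannot be undone once mothers have been turned away.

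**What to change.** - Restate the exclusion as inability to complete the outcome-collection contacts that are identical in both arms: Visit 1 and the follow-up telephone contacts. Naming Visits 1 to 6 would not do, because Table 1 attaches the intervention to some of them.
- State that inability to attend group sessions is not an exclusion, and that such mothers are enrolled, analysed by intention-to-treat and counted as non-adherent.
- Record exclusions and refusals with their reasons, and compare them by arm. The article mentions only the age of mothers who refuse.
- Reconcile Table 1, which shows PROLACT at Visits 1, 3 and 5, with the six weekly sessions described under the intervention.
- List differential consent after allocation as a limitation, since this change does not remove it.

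The cost is a change of eligibility wording, an eCRF field and a short item in site training. The downside is lower session attendance and some dilution of the effect. The reported adherence will fall too: 85% of six sessions is 5.1, so only a mother who attends all six counts as adherent.
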